## Abstract

**Background:**

Lung cancer is the leading cause of cancer-related death, and the most common cancer diagnosed globally. Approximately 85% of lung cancer cases are non-small cell lung cancer

(NSCLC). After initial surgical treatment, adjuvant therapy with conventional or targeted chemotherapy can help optimize survival. These treatments, however, must be tailored to each patients’ problematic situation, including cancer characteristics and goals of care.

Shared decision making (SDM) is a method of care by which patients and clinicians work together to form plans of care that advance the patient’s problematic human situation. This method often requires evaluating alternative options, “trying them on” for fit given their practical demands and favorable and unfavorable effects. Tools used within the encounter can facilitate and support SDM conversations, yet none exist for considering care post-surgical treatment of NSCLC.

Therefore, we aimed to evaluate the effectiveness of a novel encounter tool for SDM, NSCLC Choice, compared to usual care at improving SDM and reducing decisional conflict for patients with resected early-stage NSCLC considering adjuvant treatment.

**Methods:**

We will conduct a parallel, patient-level randomized trial comparing NSCLC Choice with usual care. Patients will be eligible if they are adults with stage >1B NSCLC eligible for postsurgical adjuvant chemotherapy. Allocation will be central and post-consent. Patients will be blinded to our trial hypothesis, instead of being invited to evaluate an educational intervention. Our primary outcome is SDM quality, which we will assess using participant reported measures (patient SDM-Q-9) obtained immediately post-encounter and an observer measure estimated from video recording of trial encounters in both arms (OPTION12). With resources to conduct a 100-patient trial, we will have >80% power to detect a 12-point medium difference between arms in patient-reported SDM-Q-9. We will also assess the secondary outcomes of knowledge about the disease and the features of treatment options using an ad hoc questionnaire, decisional conflict using the Decisional Conflict Scale, and patient and clinician satisfaction using the metrics used in prior SDM intervention trials. We will also determine encounter length using video recordings.

**Discussion:**

In testing NSCLC Choice, we seek to determine the extent to which this intervention can improve care for patients with NSCLC considering adjuvant therapy after surgery. In addition, we expect to determine whether this intervention is satisfactory to participants and feasible in practice. If successful, this study will result in an evidence-based tool for promoting patient-centered conversations around NSCLC and cancer care those fits. Trial Registration: NCT06122064
ClinicalTrials.gov

## Introduction

### Background and rationale {6a}

Lung cancer is the leading cause of cancer-related deaths, and the most common cancer diagnosed globally (1). Approximately 85% of lung cancers are non-small cell lung cancer (NSCLC)(2). The treatment of NSCLC may include the use of surgery along with conventional or targeted chemotherapy. Current guidelines recommend that the specific treatment used should be tailored to patients’ cancer characteristics. However, patient-centered cancer care requires also tailoring based on what matters to the patient. Engaging patients in shared decision making (SDM) conversations to determine what matters and what to do about a problematic situation can improve various outcomes including knowledge, satisfaction, and decision quality (3). While many tools exist to support SDM conversations, none exist to facilitate conversations around post-surgical treatment for patients with NSCLC. Therefore, we aimed to evaluate the effectiveness of a novel encounter tool for SDM, NSCLC Choice, compared to usual care at improving decisional quality and reducing decisional conflict for patients with resected early-stage NSCLC considering adjuvant treatment. (4-11)

### Objectives {7}

#### Objective 1:

To estimate the extent to which NSCLC Choice improves SDM quality compared to usual care. **Hypothesis**: Using NSCLC Choice improves SDM quality.

#### Objective 2:

To estimate the extent to which NSCLC choice reduces decisional conflict compared to usual care. **Hypothesis:** Using NSCLC Choice reduces decisional conflict.

### Trial Design {8}

We will conduct a patient-level randomized controlled trial. Participants will be randomly assigned in a 1:1 ratio to either NSCLC Choice or usual care. Figure 1 graphically illustrates the overall design of the study. All study procedures will be approved by an institutional review board (IRB # 23-003089). The trial is registered with ClinicalTrials.gov (registration number NCT06122064, registered on 30 October 2023). This protocol is reported following the SPIRIT (Standard Protocol Items: Recommendations for Interventional Trials) guidelines (see Additional file).

## Methods: participants, interventions, and outcomes

### Study Setting {9}

The trial will take place in a single Medical Oncology Department at one Academic Medical Center.

### Eligibility criteria {10}

Clinicians (physicians, nurse practitioners and physician assistants) caring for eligible patients will also be eligible for participation.

We will recruit adult patients diagnosed with NSCLC stage >1B, and deemed eligible for adjuvant treatment by their oncologist, with upcoming in-person or virtual appointments for cancer care with a participating clinician. We will exclude patients who have significant barriers to providing written informed consent or engagement in SDM, such as those patients with dementia or severe hearing or visual impairments.

#### Training personnel

After clinicians are consented, study personnel will demonstrate the intended use of NSCLC Choice. Study personnel may re-train clinicians as needed or in response to deviations in the quality of delivery observed on video recordings.

#### Who will gather informed consent {26a} and {32}

Clinicians will be recruited either during department meetings or immediately prior to an encounter with an otherwise eligible patient. Study staff will review the study with the clinician and if the clinician agrees to participate, obtain written informed consent. Study staff will approach eligible patients prior to their visit, assess their interest, and obtain written informed consent if the patient agrees to participate.

A copy of the consent form is attached as Additional file 4.

#### Consent or assent: ancillary studies {26b}

Participants may optionally consent to the future use and sharing of their data and audio/video recordings for ancillary research, as specified in the informed consent form found in additional files 4 and 5.

#### Interventions

### Explanation for choice of comparators {6b}

The comparator for this study is usual care, representing the current usual practice without the use of NSCLC Choice. This approach enables a direct assessment of the extent to which NSCLC Choice improves the quality of the decision-making process and reduces patient decisional conflict in comparison to usual clinical encounters.

#### Intervention description {11a}: NSCLC Choice Conversation Aid

The NSCLC Choice tool was developed using a human-centered design approach refined by our group over 20 years(12). Initially, we observed 13 relevant encounters to identify the challenges patients and clinicians face in deciding on post-resection adjuvant therapy for NSCLC. Based on the observations we created an initial prototype that aimed to reduce those challenges and had clinical champions use it in real, relevant encounters. Based on those observations and participant feedback, the prototype was iteratively revised and field-tested until it was judged useful, usable, and desirable by clinicians, patients, and the study team. The finalized tool (Figure 2) includes a calculator of the patient’s risk of dying within 5 years depicted in a 100-person pictograph. This shows an approximate proportion of patients who will and will not die within 5 years if they, subject to relevant clinical indications, receive (1) chemotherapy, (2) chemotherapy plus immunotherapy, (3) targeted therapy, or (4) monitoring for disease progression alone. The tool, the options it presents, and its risk display can be individualized to the patient based on PDL1>1%, EGFR mutation, and the TNM system staging. It also supports the discussion of practical considerations and adverse effects of the various options. The tool is regularly revised based on updates of clinical practice recommendations and accruing outcomes data from ongoing clinical trials. For example, as of March 2025 it includes information for use of observation, chemotherapy, immunotherapy, EGFR inhibitor and has been updated to include an adjuvant ALK inhibitor which recently received FDA approval.

The most up-to-date version of the encounter tool is available After surgery for lung cancer

### Mode of use {11d}

NSCLC Choice is designed as an encounter-based conversation aid. It was designed to support conversations rather than enforce scripted discussions. As such, the tool allows for flexibility in how and when the tool is used during the visit. Clinicians may also choose not to use the tools with certain enrolled patients, based on their professional judgment. As such we plan to assess the fidelity of use which captures not only if the tool was used but also if it was used as intended to support conversation. An assessment of intended use will be based on a previously developed instrument which will be adapted to NSCLC.

#### Usual care encounters

In usual care encounters, the clinician will conduct the encounter according to their standard care practices. The clinician will be notified prior to entering the room the patient’s allocation and if the patient is allocated to usual care will be told not to use the tool. To monitor contamination (i.e., use of the tool in patients allocated to usual care) we will video record the visit and analyze whether the tool was used as well as the extent to which behaviors supported by the tool were present. To conduct this analysis, we will modify the Observed SDM Implementation Measure (OSIM) to be specific to NSCLC Choice(13).

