#### Decisional Conflict Scale (DCS):

A 16-item scale assessing respondent uncertainty about a course of action. Each of the 16 DCS items is scored on a 0-4 Likert-type scale; the items are summed, divided by 16 and then multiplied by 25. The scale is from 0-100 where higher scores are reflective of uncertainty about the choice. There are 5 DCS subscales, where a DCS subscale consists of 3 questions (1 subscale of 4). If 2 of 3 (or 3 of the 4) questions within a subscale have responses, then the patient would be considered as a responder, and a score could be calculated. If more than one response per subscale is missing, then that specific subscale is not calculated for the patient. An overall DCS score can be calculated if no more than 5 responses are missing if each missing response falls into a different subscale. The entire scale will be administered 2 weeks post-encounter of interest and the subscales of informed, and uncertainty will be administered post encounter (16).

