#### Decision made on treatment:

derived from the recorded encounter. Decisions about whether and which therapy to follow may not be made within the encounter as the patient may wish to take some time to decide or may be contingent on test results not yet in hand (e.g. tumor mutation). In these cases, or if the final decision is not clear in the video recording, we will extract it from clinical documentation in the electronic health record (EHR).

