Data from the medical records of all enrolled patients will be abstracted to capture demographic and clinical information, covering the period from before enrollment to 6 weeks after enrollment. Data collected on patients will include variables such as Eastern Cooperative Oncology- performance status(ECOG-PS), previous treatments for NSCLC, mutations, smoking history, marital status, education, race/ethnicity, and annual income (20, 21).

In addition to data captured through surveys and EHR data, we will also capture data through video or audio recording of the clinical encounter. For in-person encounters, the study coordinator will set up the portable digital video camera at the start of a visit where both the patient and clinician have consented. The camera will be aimed at the clinician’s desk, away from the physical examination table. The clinician and the patient will be instructed on how to occlude the lens, direct the camera to a wall or turn off the camera at any time they feel this is appropriate. After the visit the study coordinator will retrieve the recording device. For virtual visits the study coordinator will join the virtual visit to record the meeting and administer the survey. After the encounter, study coordinators will transfer the video file to a secure server for analysis, deleting the recording from the device after server confirmed backup. These recordings will be used to assess SDM (OPTION) as well as contamination and fidelity intended use (OSIM).

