### Confidentiality {27}

In this study, participant privacy will be safeguarded by ensuring that no names are used on any research data (including field notes, transcriptions of conference calls, meeting recordings, audio and video recordings of interviews, and transcripts). Participants will be assigned a unique study code number for identification. The link between the code number and participant identity will be stored in a secure, firewalled spreadsheet on a research server, accessible only to study investigators and study staff, all of whom have human subjects research certification. This spreadsheet will be deleted once all participant follow-up is complete. A do-not-call list will be maintained for individuals who decline participation to prevent multiple contact attempts, as patients may have several appointments at participating clinics during the study. All research materials will be stored securely on a server or in locked file cabinets, and all materials will be destroyed seven years after the study’s completion.

Digital recordings of clinical encounters will be immediately uploaded to the research team’s secure server and deleted from portable devices after overnight back-up of servers. The video and audio files will be identified using a code number that does not include the name of the clinician, support staff, or patient or reference to their medical record number or date of birth. The research data is only accessible with password protected and logged access.

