**Patient Forms/Schedule**					
Informed Consent	X				
Index Encounter Survey^1^			X		
Follow-up survey^2^				X	
EMR Review			X		X
Video recording^3^		X			

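### Usual-care contamination is checked only at the recorded index visit, but the full decisional conflict score for Objective 2 is taken 2 weeks later, so tool use in between would dilute that contrast without being reported

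*Protocol article*

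**What the plan says.** All references are to the protocol article.

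- **Instruction.** Under Usual care encounters, the clinician learns the allocation just before going into the room and "if the patient is allocated to usual care will be told not to use the tool".
- **Contamination.** The same section defines it by patient: any tool use with someone assigned to usual care. The method of detection is "we will video record the visit and analyze whether the tool was used". Section {18a} gives this task to the encounter recordings: "These recordings will be used to assess SDM (OPTION) as well as contamination and fidelity intended use (OSIM". Table 1 marks recording under the index encounter and nowhere else.
- **Objective 2.** "To estimate the extent to which NSCLC choice reduces decisional conflict compared to usual care". On timing, the DCS paragraph of Outcomes {12} says: "The entire scale will be administered 2 weeks post-encounter of interest". Only the Informed and Uncertainty subscales are also collected straight after the encounter (same paragraph; Table 1, footnote 1).
- **Open decisions.** The paragraph on the treatment decision says: "Decisions about whether and which therapy to follow may not be made within the encounter". In that case the decision is taken from the health record, which is reviewed to 6 weeks.
- **Who sees whom.** Randomization is by patient and stratified by clinician {16a}, so the same clinicians treat both arms. All of them are shown how to use the tool (Training personnel).

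**The concern.** The definition of contamination, the way it is detected and the timing of the outcome do not cover the same period. The definition has no time limit, detection covers one visit, and the total score for Objective 2 comes 2 weeks after that visit. A usual-care patient whose decision is still open may speak again with a clinician who knows the tool. If the tool is used then, the patient answers the 2-week DCS as someone exposed to it but is analysed, correctly under intention to treat, in the usual-care arm.

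The result would be a smaller arm difference together with a contamination report that looks clean because it covers only the index visit. A null result for Objective 2 could then be read as no effect of the tool on decisional conflict, when part of the explanation might be crossover that nobody recorded. Exposure not asked about at 2 weeks is hard to reconstruct afterwards.

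**Working it through.** **1. Set the windows side by side.**

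| Element | Period covered | Source |
|---|---|---|
| Contamination, as defined | No limit; any tool use in a usual-care patient | Usual care encounters |
| No-tool instruction, as described | Entry to the index visit; no end date given | Usual care encounters |
| Contamination, as measured | Recorded index visit | Usual care encounters; {18a}; Table 1 |
| SDM-Q-9, OPTION12, DCS Informed and Uncertainty | Index visit and the survey that follows it | {12}; Table 1 |
| Entire DCS | 2 weeks after the index visit | {12}; Table 1, footnote 2 |
| Treatment decision | Index visit, else health record to 6 weeks | {12}; {18a} |

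The 2-week survey holds confirmation of the decision, the DCS and satisfaction (Table 1, footnote 2). It has no exposure item, and the record review is not assigned that task.

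**2. Can the early subscales supply a total?** No. The DCS has 16 items: four subscales of 3 and one of 4. Two subscales hold 6 or 7 items, which leaves 10 or 9 unanswered. The scoring rule in {12} allows at most 5 missing, each in a different subscale.

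**3. Reproduce the plan's own power.** Inputs from {14}: difference 12, SD 20, 50 per arm, two-sided alpha 0.05, ICC 0.01, 5 patients per clinician (alternative: 10).

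- Design effect = 1 + (m − 1) × ICC: 1 + 4 × 0.01 = 1.04, or 1 + 9 × 0.01 = 1.09.
- Effective n per arm: 50/1.04 = 48.1, or 50/1.09 = 45.9.
- Power ≈ Φ(δ / (σ√(2/n)) − 1.96). For m = 5: 12 / (20 × √(2/48.1)) = 2.94, and Φ(0.98) = 83.7% (noncentral t 82.9%; the plan states 82%). For m = 10: 82.0% (noncentral t 81.1%; the plan states 80%).

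Both agree within 2 points. The point here does not rest on an error in the sample size.

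**4. Dilution.** Let c be the share of usual-care patients exposed before the 2-week DCS, and suppose late exposure gives the full tool effect. The usual-care mean becomes (1 − c) × unexposed mean + c × exposed mean, so the arm difference is multiplied by (1 − c). The plan gives no effect, SD or crossover rate for the DCS. The standardized effect 12/20 = 0.6 is borrowed from SDM-Q-9 as an assumption.

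| c (assumed) | Effect, SD units | Power, design effect 1.04 | Power, design effect 1.09 | Factor on N, 1/(1 − c)² |
|---|---|---|---|---|
| 0% | 0.60 | 83.7% | 82.0% | 1.00 |
| 5% | 0.57 | 79.8% | 77.9% | 1.11 |
| 10% | 0.54 | 75.4% | 73.4% | 1.23 |
| 20% | 0.48 | 65.3% | 63.3% | 1.56 |
| 30% | 0.42 | 54.0% | 52.1% | 2.04 |

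**5. Softer assumption.** If late exposure gives only a fraction f of the effect, the multiplier is 1 − cf. With c = 20% and f = 0.5 it is 0.90, the same as the 10% row. The table is therefore the worst case for each c.

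**The case against.** Much of the case on the other side is right, and it limits the point.

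- **Deferred decisions and repeat visits.** A reader might infer that the plan expects most decisions to be deferred and patients to return soon. It says only that a decision may fall outside the encounter. The remark in Confidentiality {27} that "patients may have several appointments at participating clinics during the study" explains a do-not-call list for people who decline. It is no evidence about enrolled patients. No section gives the frequency or timing of a second visit.
- **Prevention.** A reader might infer that nothing stops later use. That is too strong. Allocation is by patient and the instruction has no stated expiry, so a clinician may well treat it as standing. What the text supports is that the instruction is described only at entry to the index visit, and that later use is not monitored.
- **Primary outcome.** A reader might infer that the trial's main result is at risk. It is not. SDM-Q-9 and OPTION12 concern the index encounter. The two early DCS subscales are also protected when the survey is completed straight after the visit, as {18a} intends. They would show an early difference even if it faded by 2 weeks.
- **Size.** The power figures borrow an effect from another scale, take late exposure at full strength and assume the crossover share. The trial is powered on SDM-Q-9, not on the DCS.
- **Level of detail.** Survey items and abstraction fields are often left to a full protocol. But this article does state the definition, the data source, the survey contents and the schedule, and these do not match one another. That goes beyond missing detail.

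**Conclusion.** The point holds for the 2-week DCS. As written, tool use with a usual-care patient between the index visit and the 2-week survey would bias that contrast towards zero and would not appear in the contamination report. The direction follows from the design, provided the tool does lower decisional conflict. The size is unknown because the documents give no crossover rate. The fall from about 84% power to about 75% at 10% exposure and about 65% at 20% is an illustration, and it rests on the 0.6 SD effect and full late exposure.

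The treatment decision is a separate secondary endpoint, not part of Objective 2. It is open to the same unrecorded exposure, over up to 6 weeks. It has no stated direction of effect, so the dilution formula is not applied to it.

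This is a cheap improvement that decides how a null Objective 2 result can be interpreted. It does not threaten the primary endpoint.

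**What to change.** 1. In Usual care encounters, state that the no-tool instruction applies to every encounter of a usual-care patient until the 2-week survey is completed, and define contamination over the same window.
2. Add one yes/no item to the 2-week survey, placed after the DCS so that it cannot influence those answers, asking whether the patient has been shown or has used the tool since the index visit.
3. In the record review already planned, note later visits with participating clinicians. This shows opportunity rather than use, but it also covers the treatment-decision endpoint to 6 weeks.
4. Report exposure by arm, and read the 2-week DCS alongside the post-encounter Informed and Uncertainty subscales.
5. Reconcile section {18a}, which lists the DCS in the post-encounter survey without limit, with Outcomes {12} and Table 1, footnote 1, which restrict it to two subscales. If the full scale were in fact given then, an undiluted total would exist and the concern would be smaller.

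The cost is protocol wording, one survey item and a standing allocation reminder for clinicians, with no extra patients or recordings. The downside is a slightly longer form and a longer period in which usual-care patients go without the tool.
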